### Plans to give access to the full protocol, participant level-data, and statistical code {31c}

After publication of the results of the trial, the data will be made partially accessible to other investigators. Data access request will be reviewed by the Trial Steering Committee that will grant access or not. To gain access, requestors will be required to sign a data access agreement. Statistical code developed for the analysis of the trial can be made accessible by request to the biostatisticians of the study.

## Oversight and monitoring

### Composition of the coordinating center and trial steering committee {5d}

This study will be conducted in a manner consistent with Good Clinical Practice. The steering committee will be composed of 5 co-authors (MR, HY, JCR, LB, MM). Drs. HY, JCR, LB, and MM will oversee all research activities. The study coordinator (HY) will be responsible, in part, for the communication with all investigators. The team leader (JCR), project manager ([name]), and study coordinator (HY) will hold weekly meetings, and full team meetings will be held monthly. There will be no endpoint adjudication committee, as the composite primary endpoint of the study was neither complex nor subjective (VFD and survival).

### Adverse event reporting and harms {22}

Based on the pilot trial on 34 patients [8], the following adverse events are suspected to increase or decrease in association with the intervention: severe mixed acidosis, ventilator-associated pneumonia, acute cor pulmonale, and barotrauma. These expected adverse events will be collected systematically and daily in the eCRF from day 1 to day 28 of the study as long as the participants remain mechanically ventilated. Given their high frequency in relation with the severity of the underlying disease, the following non-serious adverse events will not be reported: acute kidney injury with KDIGO grade < 3, metabolic disorders, non-fatal nosocomial infections (with the exception of bacteremia and ventilator-associated pneumonia), shock (with the exception of those related to acute cor pulmonale), non-fatal worsening of respiratory condition, and ICU-acquired weakness. All other adverse events occurring from inclusion to hospital discharge will be reported through a spontaneous report.

Serious adverse event (SAE) information will be collected for the duration of the participant’s involvement in the trial. SAEs will be managed according to the best current standard of care and reported to the sponsor according to good clinical practices. All SAEs will be reported to the sponsor within one business day, in a structured narrative explaining the events that occurred. An internal safety monitor will adjudicate all SAEs for report completeness, seriousness of event, and relationship to study interventions. After receiving an unexpected SAE report, the sponsor will notify to the French regulatory agencies and the research ethics committee (CPP Ile de France 7).

Expected adverse events, SAEs, and non-serious adverse events will be reported in trial publication.

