ULTV without extracorporeal circulation is an appealing technique to protect the ARDS lung in the context of a worldwide pandemic, as it does not require any material and consumables, and may be applied in low- to middle-income countries. We hypothesized that ULTV without extracorporeal circulation is a credible option to reduce COVID-19 mortality and duration of mechanical ventilation, in patients with severe and moderately severe ARDS [2].

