### Objectives {7}

The main objective is to assess the benefit of ULTV in comparison with protective ventilation on a composite primary endpoint that will include the all-cause mortality at day 90 as the prioritized criterion and the number of days free from invasive mechanical ventilation (VFD) at day 60 as the second criterion.

The following are the secondary objectives:
To test whether ULTV is associated with a decrease in ARDS all-cause mortality at day 90 after inclusionTo test whether ULTV is associated with higher VFD at day 60 after inclusionTo test whether ULTV is associated with a decrease in time to successful extubationTo test whether ULTV is associated with a shorter hospital stayTo test whether ULTV impacts the following respiratory parameters assessed daily from inclusion to weaning of deep sedation or 14 days after inclusion whichever comes first (PaO_2_/FiO_2_ ratio, pH, PaCO_2_, positive end-expiratory pressure (PEEP), VT, total PEEP, plateau pressure, driving pressure, respiratory rate, mechanical power (MP))To test whether ULTV is associated with an increase in sedation dose during the first 14 days after inclusionTo test whether ULTV is associated with an increase in rescue therapy during the first 14 days after inclusionTo test whether ULTV is associated with a decrease in the incidence density rate of adverse events during the first 28 days after inclusion (severe mixed acidosis, ventilator-associated pneumonia, acute cor pulmonale, barotrauma, any serious adverse events)To test whether ULTV is associated with cognitive impairment at day 365 after inclusionTo test whether ULTV is associated with quality-of-life impairment at day 365 after inclusionTo test whether ULTV is associated with post-traumatic stress disorder at day 365 after inclusionTo evaluate the efficiency of the innovative strategy performing a cost-effectiveness analysis at day 90 after inclusion

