6.Value of daily sedation dose (midazolam, propofol, and opioid) during the first 14 days after inclusion.Opioid doses will be expressed as morphine equivalent (1 mg fentanyl = 100 mg morphine, 1 mg sufentanil = 1000 mg morphine).7.The use of rescue therapy (i.e., muscle relaxant, prone position, inhaled nitric oxide, recruiting maneuvers, ECMO) during the first 14 days after inclusion.8.Severe mixed acidosis, ventilator-associated pneumonia, acute cor pulmonale, barotrauma, and any serious adverse events during the first 28 days after inclusion.Severe mixed acidosis will be defined as the association of pH < 7.15 and PaCO_2_ > 45 mmHg.Ventilator-associated pneumonia will be reported as clinically diagnosed by the attending physician.Acute cor pulmonale will be defined as the association of right ventricle dilatation (right ventricle surface/left ventricle surface > 0.6) and septal dyskinesia assessed by echocardiography.Barotrauma will be defined as the occurrence of any pneumothorax, pneumomediastinum, subcutaneous emphysema, or pneumatocele of more than 2 cm.Serious adverse event will be defined as any adverse event resulting in death, leading to a life-threatening condition, resulting in hospitalization or prolongation of hospitalization, resulting in disability or permanent damage, and resulting any other important medical event.9.Montreal Cognitive Assessment (T-MoCA) test [15] assessed by a phone call at day 365 after inclusion.10.SF-36 score [16] assessed by a phone call at day 365 after inclusion.11.IES-R score [17] assessed by a phone call at day 365 after inclusion.12.Incremental cost-effectiveness ratios of the innovative strategy compared to the reference strategy at day 90 after inclusion.

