### Sample size {14}

The sample size was computed through data simulations based on the following hypotheses:
Ninety-day mortality 45% in the control group, and 40% in the intervention group (i.e., relative reduction 11%)Mean ± standard deviation (*SD*) VFD at day 60 28 ± 16.5 in the control group and 34.5 ± 13 in the intervention group

The expected mortality in patients with COVID-19 and moderate to severe ARDS is between 34 and 50% [1]. The mean and *SD* of VFD at day 60 in the control group was taken from the subgroup of patients with PaO_2_/FiO_2_ < 150 mmHg included in the control group of the prospective randomized Xtravent-study comparing ultra-protective ventilation with extracorporeal CO_2_ removal versus conventional protective ventilation [7]. To be conservative, we have chosen to take an expected difference between the two groups of the present study corresponding to 50% of the difference observed in the Xtravent-study between the control and the intervention groups.

For each scenario corresponding to a given sample size, 1000 datasets were simulated. For each simulation, the score was computed for each patient and compared between the two groups using the test of Mann and Whitney. The power was computed as the proportion of tests with a bilateral *p*-value < 0.05.

The results of the simulations allowed us to determine that the inclusion of 100 patients per group will achieve a power greater than 80% to conclude a significant difference between the groups.

The simulations were implemented by two biostatisticians with the SAS software, version 9.4 (Copyright (c) 2002–2003 by SAS Institute Inc., Cary, NC, USA) and the R software, version 3.6.1 (R Core Team (2012)). The results were similar.

To account for premature exits from the study (withdrawal of informed consent for example), we have planned to add 10% more patients (10 supplementary patients in each group for a total of 220 patients).

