## Data collection and management

### Plans for assessment and collection of outcomes {18a}

Investigators are responsible for the assessment and collection of outcomes, baseline, and other trial data. Data will be entered in the electronic case report form by delegated team members and will be monitored by trained clinical research associates. The digital version of the case report form is provided in Additional file 6. Subjects will be assessed daily while hospitalized in the intensive care unit (ICU). Day 60 assessment will be performed by investigators or delegated team members using electronic medical records and phone calls to the patient’s general practitioner and to any MD involved in patient care after ICU discharge if required. Day 365 assessment will be performed by a phone call by investigators or delegated team members, to administer 3 tests whose validity have been proven when administered remotely [15, 18, 19]. French language versions of T-MOCA [15], IES-R [17], and SF-36 [16] questionnaires will be implemented in the electronic case report form and are provided in Additional files 7, 8, and 9.

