#### Analysis of the secondary outcomes

The analysis of the secondary objectives will also be carried out by intention to treat. Qualitative secondary outcomes such as the mortality at day 90 will be described in each group by the event proportion and compared using the *χ*^2^ test or the exact test of Fisher. Quantitative secondary outcomes such the VFD at day 60 will be described in each group by the mean and the standard deviation or the quartiles, and the minimum and maximum values according to the shape of the distribution. They will be compared between the two groups using the *t* test of Student or the test of Mann and Whitney.

All the analyses will be carried out using the SAS software, version 9.4 (Copyright (c) 2002–2003 by SAS Institute Inc., Cary, NC, USA). The comparisons will be considered statistically significant for a bilateral *p*-value < 0.5.

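### Four named harms are defined over 28 days from inclusion but collected systematically only during ventilation, so non-serious events after extubation are ascertained less well, and earlier in the arm extubated sooner

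*Protocol article*

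**What the plan says.** Three sections of the protocol article bear on the window for the four named harms.

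- **Objectives {7}** asks whether ULTV is associated with a "decrease in the incidence density rate of adverse events during the first 28 days after inclusion". It names a person-time measure but no denominator.
- **Secondary outcomes**, item 8, lists "Severe mixed acidosis, ventilator-associated pneumonia, acute cor pulmonale, barotrauma, and any serious adverse events during the first 28 days after inclusion". No ventilation condition is attached. The definition of barotrauma (pneumothorax, pneumomediastinum and so on) and the echocardiographic definition of acute cor pulmonale do not require the patient to be ventilated.
- **Adverse event reporting and harms {22}** has the four events entered each day, "from day 1 to day 28 of the study as long as the participants remain mechanically ventilated".

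The same harms section has two wider channels. Serious adverse events are collected throughout trial participation, and other adverse events are reported spontaneously up to hospital discharge.

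For the analysis, **Analysis of the secondary outcomes** says that qualitative outcomes will be "described in each group by the event proportion and compared using the" chi-square or Fisher test. It does not mention a rate.

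**The concern.** The outcome has a fixed window and the data collection has a variable one. The variable window closes at extubation, which comes after randomisation and is itself a trial outcome. The Background section presents ULTV as a "credible option to reduce COVID-19 mortality and duration of mechanical ventilation", so if the hypothesis is right, collection closes earlier in the ULTV arm.

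From that point, a non-serious named event is no longer sought daily. It is recorded only if someone volunteers it. It is not even clear that the spontaneous route applies, because that route is worded for events other than the four. Staff and outcome assessors know the allocation (Who will be blinded {17a}).

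If such events are then counted over 28 days, whether as a proportion or over 28 days of person-time, the days after extubation enter as event-free unless a report happens to be made. This would understate harms in both arms, and more so in the arm extubated sooner. These are the events that the protocol itself singles out as likely to move, up or down, with the intervention.

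**Working it through.** The document gives no figure for these harms, so there is none to reproduce. The finding rests on the texts set out above; the arithmetic only shows its scale.

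**Inputs.** Sample size {14} gives ventilator-free days (VFD) at day 60 of "28 ± 16.5 in the control group and 34.5 ± 13 in the intervention group", and 90-day mortality of 45% (control) and 40% (ULTV).

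**Assumptions, not in the document.** The VFD figures apply to survivors and are roughly normal, clipped to 0–60. Ventilation is continuous.

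**Step 1: who leaves collection before day 28.** Ventilated days are x = 60 − VFD, so x < 28 means VFD > 32.
- Control: z = (32 − 28)/16.5 = 0.24, share above = 40%.
- ULTV: z = (32 − 34.5)/13 = −0.19, share above = 58%.

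With VFD rounded to whole days the shares are 39% and 56%.

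**Step 2: collected days among survivors.** The mean of min(28, x), by simulation of 1,000,000 patients per arm, is 23.4 (control) and 21.6 (ULTV). The ratio is 0.92, or about 8% fewer days. Uncollected days are 28 − 23.4 = 4.6 and 28 − 21.6 = 6.4, which is 16.5% and 22.9% of the window.

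**Step 3: add deaths,** each assumed to contribute 10 to 20 collected days in either arm.
- 10 days: control 0.55 × 23.4 + 0.45 × 10 = 17.4; ULTV 0.60 × 21.6 + 0.40 × 10 = 17.0. Gap about 2%.
- 20 days: control 12.87 + 9 = 21.9; ULTV 12.96 + 8 = 21.0. Gap about 4%.

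The gap shrinks because longer survival in the ULTV arm offsets earlier extubation. It does not mean that fewer events after extubation are missed.

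**Step 4: separate real effect from bias, in survivors.** Let the event rate be the same in both arms: h per ventilated day and f × h per day after extubation, with nothing recorded after extubation (the worst case).
- Recorded ratio, ULTV to control: 21.6/23.4 = 0.923.
- True 28-day ratio: (21.6 + 6.4f)/(23.4 + 4.6f).

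| f (assumed) | True ratio | Recorded ÷ true |
|---|---|---|
| 0 | 0.923 | 1.00 |
| 0.10 | 22.24/23.86 = 0.932 | 0.99 |
| 0.25 | 23.20/24.55 = 0.945 | 0.98 |
| 1 | 28/28 = 1.00 | 0.92 |

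At f = 0 the lower count in the ULTV arm is wholly real, because less ventilated time means fewer events. The full 8% becomes bias only if the daily risk after extubation equals that during ventilation and every such event goes unrecorded.

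**Step 5: choice of measure.** With an equal rate confined to ventilated time (h = 0.01 per day), event proportions are 20.6% and 19.1%, ratio 0.93. Over h = 0.005 to 0.03 the ratio is 0.93 to 0.94. The rate per ventilated day gives 1.00. The answer thus depends on the denominator, which the Objectives leave open.

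**The case against.** The strongest reply is that little is lost. Serious events after extubation are collected without any ventilation condition, and the seriousness definition is broad. Ventilator-associated pneumonia and severe mixed acidosis arise mainly during ventilation. The allocated strategy itself ends at weaning from deep sedation, so collection already outlasts it. A patient who is reintubated is ventilated again and plausibly back under daily collection. The Objectives also name an incidence density rate, a measure made for unequal observation time. Its exact denominator may properly sit in the analysis plan or the full protocol, which are not shown.

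Most of this stands, and it rules out two stronger readings. A reader might infer that events after extubation are simply missed. The text does not support that, because the serious ones have their own channel. A reader might also take the 8% as the bias in favour of ULTV. It is a difference in collected days among survivors, and part or all of the matching difference in events would be a true consequence of shorter ventilation.

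What the reply does not remove is the mismatch between two stated windows. A ventilated-day denominator corrects for exposure, but it cannot recover non-serious events that were never recorded, and it answers a different question from the 28-day outcome as written.

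**Conclusion.** The point holds in limited form. The stated collection rule does not match the stated outcome. For non-serious barotrauma and acute cor pulmonale after extubation, ascertainment falls from daily entry to spontaneous reporting at most. The switch comes earlier in whichever arm is extubated sooner, and staff know the allocation.

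The effect is modest. The gap in collected days is about 8% among survivors (design VFD taken as normal in survivors) and about 2 to 4% with deaths included (10 to 20 days each, assumed). The document gives no basis for estimating the number of missed events. The direction favours the arm extubated sooner, which is the ULTV arm if the hypothesis is right. The primary outcome is not affected.

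**What to change.** In Adverse event reporting and harms {22}, collect the four named events to day 28 regardless of ventilation status: daily while the patient is in the ICU, and from the hospital record after that. This matches the window in Objectives {7} and Secondary outcomes. State the denominator of the incidence density rate as observed days to day 28 or death.

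If collection is to remain limited to ventilation, restate the outcome in both sections as events during ventilation per ventilated day, and do not present it as a 28-day proportion.

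The cost is a few more eCRF days for each extubated ICU patient and one chart check at day 28. Patients are already assessed daily in the ICU (Plans for assessment and collection of outcomes {18a}), so no new visit or test is needed. For patients already enrolled, the chart check can be done retrospectively. It will find acute cor pulmonale only where an echocardiogram was done. If the full protocol already records these events to day 28, only the article's wording needs correcting.

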### Frequency and plans for auditing trial conduct {23}

This study will be conducted in a manner consistent with Good Clinical Practice and within the French regulatory framework. Trial conduct will be regularly audited by the sponsor (Hospices Civils de Lyon) independently from the investigators, checking for the following items:
Verification of the validity of informed consent by every trial participantIdentification of any violation in the trial proceduresQuality control of data reporting in the digital case report formQuality control of serious adverse events reporting

An inspection or audit may also be performed by regulatory authorities. Inspectors will check the documents, logistics, records, and any other resources the authorities consider to be associated with the clinical trial and that may be located at the trial site itself.

### Composition of the data monitoring committee, its role, and reporting structure {21a}

The data monitoring committee (DMC) is composed of 3 experts independent from the coordinating investigators and its institution, with expertise in conducting clinical trials, experience in serving on other DMC, and absence of financial or intellectual conflicts of interests with the sponsor and investigators of the present trial. The 3 experts are Pr. [name] (biostatistician, CHU Dijon), Pr. [name] (intensivist, CHU Nice), and Pr. [name] (intensivist, CHU Montpellier). The DMC operated within the framework of the charter provided in Additional file 10. After the first meeting at the beginning of the trial, the DMC will reunite after the occurrence of the first 30 deaths among the study participants, every 30 deaths thereafter until study completion, and at least every 6 months during the study. Additional DMC meetings will be convened as needed.

### Plans for communicating important protocol amendments to relevant parties (e.g., trial participants, ethical committees) {25}

Important protocol modifications will have to be approved by the research ethics committee (CPP Ile de France 7) and French regulation agencies. After approval, protocol modifications will be signaled to the trial registry, investigators, and participants in the trial.

### Dissemination plans {31a}

This trial is registered with the publicly accessible www.clinicaltrials.gov registry for dissemination and data sharing purposes (NCT04349618). Its results will be published in a high-impact, peer-reviewed journal no more than 12 months after the end of the last participant visit at day 90 and made freely available for public access within 6 months of publication. A second publication reporting long-term follow-up at day 365 after inclusion is planned. The investigators will follow the rules and guidelines of the International Committee of Medical Journal Editors [21] for authorship. In practice, the steering committee will be among the authors of the publication, as will the investigators who included the patients in the trial. We expect to prepare additional publications addressing the different facets of this work. We will also present our results at national or international scientific conferences.

## Discussion

We had two practical concerns at the time of the study design. The first concern was related to a possible low inclusion rate. Indeed, the research ethic committee initially denied the possibility of co-inclusion in the present trial and in any clinical trial involving unlicensed new drugs or medical devices. As most intensive care units in France were participating in multiple drug trials testing antiviral or immunomodulatory drugs against COVID-19 pneumonia, we anticipated that the study would require at least 1 year for completion.

The second concern was related to the limited study funding, limiting the number of participating centers and restraining the geographical area of participating centers to limit monitoring costs.

## Trial status

This trial is ongoing. Enrollment began on April 15, 2020, and is expected to be completed on April 15, 2021.

## Abbreviations

ARDS: Acute respiratory distress syndrome
BAL: Broncho-alveolar lavage
DMC: Data monitoring committee
ECCOR: Extracorporeal CO_2_ removal
ECMO: Extracorporeal membrane oxygenation
FiO_2_: Fraction of inspired oxygen
ICU: Intensive care unit
IES-R: Impact of event scale - revised
MP: Mechanical power
PaCO_2_: Carbon dioxide partial pressure in the arterial blood
PaO_2_: Oxygen partial pressure in arterial blood over fraction of inspired oxygen
PBW: Predicted body weight
PEEP: Positive end-expiratory pressure
RASS: Richmond agitation sedation scale
T-MoCA: Telephonic Montreal cognitive assessment test
ULTV: Ultra-low tidal volume ventilation
VFD: Ventilator-free days
VT: Tidal volume
